### Data collection

#### Clinical variables

At inclusion visit between 12 and 22 weeks, demography, medical and family history and current pregnancy health information are collected. Anthropometric variables (weight and height) are measured; blood and urine samples are drawn. No additional follow-up visit is required, as women benefit of the usual care for pregnancy (according to the French guidelines) which consists of 7 prenatal visits and 1 post-natal visit between 6 and 10 weeks after delivery. Information is collected from maternal medical records regarding health during pregnancy including gestational hypertension, preeclampsia and GDM. All women in both groups undergo a 75 g-oral glucose tolerance test (75 g glucose oral load after a fasting period of 10 h minimum) between 24 and 28 weeks. The diagnosis of GDM is made according to the IADPSG criteria (i.e. fasting plasma glucose ≥5.1 mmol/L [0.92 g/L] and/or 1-h glucose ≥10 mmol/L [1.80 g/L] and/or 2-h glucose ≥8.5 mmol/L [1.53 g/L]). The beginning of labor and the delivery mode are collected as well as the occurrence of post-partum hemorrhage. Neonatal and postnatal outcomes include the occurrence of traumatism due to childbirth, Apgar score, umbilical cord pH, admission to neonatal unit and use of phototherapy for hyperbilirubinemia. To address the influence of the intervention on neonatal growth and adiposity, neonatal anthropometric variables (weight, length, adiposity skinfolds) are measured within the first 24 h. At the post-natal visit, maternal demographic data, health since the delivery (post-partum complications such as fever, hemorrhage, thromboembolic events) and duration of breastfeeding are obtained. Maternal anthropometric variables (weight, height) are measured. To address the safety and the impact of the intervention on child health, details regarding the health since birth is also obtained. To address the influence of the intervention on infant adiposity, infant length and weight are measured at birth.

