**Methods:**

Electronic-Personalized Program for Obesity during Pregnancy to Improve Delivery (ePPOP-ID) is an open multicenter randomized controlled trial which will assess the efficacy of an e-health web-based platform offering a personalized lifestyle program to obese pregnant women in order to reduce the rate of labor procedures and delivery interventions in comparison to standard care. A total of 860 eligible pregnant women will be recruited in 18 centers in France between 12 and 22 weeks of gestation, randomized into the intervention or the control arm and followed until 10 weeks of postpartum.

The intervention is based on nutrition, eating behavior, physical activity, motivation and well-being advices in which personalization is central, as well as the use of a mobile/tablet application. Inputs includes data from the medical record of participants (medical history, anthropometric data), from the web platform (questionnaires on dietary habits, eating behavior, physical activity and motivation in both groups), and adherence to the program (time of connection for the intervention group only). Data are collected at inclusion, 32 weeks, delivery and 10 weeks postpartum. As primary outcome, we will use a composite endpoint score of obstetrical interventions during labor and delivery, defined as caesarean section and instrumental delivery (forceps and vacuum extractor). Secondary outcomes will consist of data routinely collected as part of usual antenatal and perinatal care, such as GWG, hypertension, preeclampsia, as well as fetal and neonatal outcomes including premature birth, gestational age at birth, birth weight, macrosomia, Apgar score, arterial umbilical cord pH, neonatal traumatism, hyperbilirubinemia, respiratory distress syndrome, transfer in neonatal intensive care unit, and neonatal adiposity. Post-natal outcomes will be duration of breastfeeding, maternal weight retention and child weight at postnatal visit.

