To our knowledge, there is no published work that studied the effect of a technologically based intervention during the pregnancy. A program was recently tested in the post-partum period. The Diabetes Prevention Program demonstrated that an intensive, face-to-face lifestyle intervention could achieve weight loss and reduce incidence of type 2 diabetes in middle-aged adults at high-risk, including women with a GDM history [25]. However, because face-to-face lifestyle intervention studies in post-partum women have had limited success [25, 26] and given the multiple barriers to face-to-face interventions, and the widespread use of the Internet, the authors adapted the Diabetes Prevention Program into a web-based lifestyle intervention using web-based technology to deliver lifestyle interventions for women with recent GDM. The study demonstrated the feasibility and efficacy of the web-based lifestyle modification program to decrease postpartum weight retention in the first postpartum year for women with recent GDM. The authors concluded that this program is at low cost to implement and has potential for broad dissemination [19]. These data suggest that a web-based program should be tested in obese pregnant women to limit GWG.

The purpose of our study is to assess the efficacy of an e-personalized program including antenatal dietary and lifestyle advices in pregnancy to reduce the rate of labor procedures and interventions in comparison to standard care. As secondary objectives, we will investigate whether the e- program may improve the health of the mothers and their newborns, compared to a control group allocated to standard care. Maternal secondary outcomes include reducing GWG, increasing the proportion of participants having a GWG within the guidelines, reducing the risk of hypertension, preeclampsia, and GDM, reducing fat and sugar intake, increasing physical activity, increasing breastfeeding and duration, reducing weight retention after childbirth. For newborns, secondary outcomes will consist of improving birth weight, reducing risk of macrosomia, trauma associated with childbirth and low Apgar score, reducing the use of phototherapy for hyperbilirubinemia, as well as reducing number of admissions to neonatal intensive care unit and number of infants with excessive weight at postnatal visit.

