### Endpoints

The primary endpoint consists of the rate of obstetrical interventions during labor and delivery, defined as caesarean section and instrumental delivery (forceps and vacuum extractor). As secondary endpoints, we include data routinely collected as part of usual antenatal and perinatal care, such as GWG (measured with a scale at each visit), gestational hypertension (defined as systolic blood pressure ≥ 140 mmHg and/or diastolic blood pressure ≥ 90 mmHg after 20 weeks), preeclampsia (defined as gestational hypertension and proteinuria ≥0.30 g/24 h), GDM (diagnosed by a 75 g-oral glucose tolerance test between 24 and 28 weeks according to the guidelines of the International Association of the Diabetes and Pregnancy Study Groups (IADPSG)). Fetal and neonatal collected outcomes, consist of premature birth (defined as birth before 37 weeks), gestational age at birth, birth weight, rate of macrosomia (defined as birth weight > 90th percentile for gestational age), Apgar score, arterial umbilical cord pH, neonatal traumatism, hyperbilirubinemia, respiratory distress syndrome (i.e. needs for oxygen) and transfer in neonatal intensive care unit. Post-natal outcomes are duration of breastfeeding, maternal weight retention and child weight at the postnatal visit (8 ± 2 weeks’ post-partum).

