### Statistics

Statistical analyses will be independently performed by the Biostatistics Department of University of Lille. Data will be analyzed using the SAS software (SAS Institute Inc., Cary, NC, USA) and all statistical tests will be performed with a 2-tailed alpha risk of 0.05. A detailed statistical analysis plan will be written and finalized prior to the database lock. For each exploratory analysis, a statistical analysis plans will be provided before any data analysis. Baseline characteristics will be described for each group. Quantitative variables will be expressed as mean (± standard deviation), median (± interquartile range) and 95% confident interval. Qualitative variables will be expressed as frequencies and percentages. Normality of distribution will be assessed graphically and using the Shapiro-Wilk test. The primary analysis for primary and secondary endpoints will be conducted on the intention-to-treat principle. A secondary per-protocol analysis will be performed.

The primary endpoint (rate of delivery interventions) will be compared between the two groups using the Chi-square test. Absolute and relative risk difference (intervention vs. control) and their 95% confidence intervals will be calculated. For the secondary objectives, binary endpoints will be compared between the two groups using chi-square tests or Fisher’s exact tests when the expected cell frequency will be inferior to 5. Quantitative endpoints will be compared between the two groups using student *t* tests or Mann-Whitney U tests in case of non-normal distribution (except if a log-transformation can be applied to normalize the data). For quantitative endpoints involving repeated measures, a linear mixed model will be used. This model allows to perform an ANOVA for repeated measures taking into account the correlation between the repeated measures. The choice of the covariance in the models will be based on the AIC criteria and normality of residuals will be checked.

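### Infant weight is an outcome at the postnatal visit, but the data-collection text times its measurement at birth; the wording should be reconciled and the comparison standardised for age

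*Protocol article*

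**What the plan says.** Three places in the protocol article set an infant outcome at the postnatal visit:

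- Abstract, Methods: "Post-natal outcomes will be duration of breastfeeding, maternal weight retention and child weight at postnatal visit".
- Background, last paragraph (secondary objectives): a reduction in the "number of infants with excessive weight at postnatal visit".
- Endpoints: "maternal weight retention and child weight at the postnatal visit (8 ± 2 weeks" post-partum).

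The Clinical variables section under Data collection says when measurements are taken. For the newborn, "neonatal anthropometric variables (weight, length, adiposity skinfolds) are measured within the first 24 h". For the postnatal visit, placed between 6 and 10 weeks after delivery, it states "Maternal anthropometric variables (weight, height) are measured" and adds that details of the child's health since birth are obtained. The paragraph then ends with "To address the influence of the intervention on infant adiposity, infant length and weight are measured at birth".

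For the analysis, the Statistics section says "Quantitative endpoints will be compared between the two groups using student" t tests, or Mann-Whitney tests if the distribution is not normal. Repeated quantitative measures get a linear mixed model. Age at the visit is not mentioned.

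**The concern.** The stated measurement time does not match the stated outcome time. A weight taken at birth cannot supply a weight at about 8 weeks. A site working from the Clinical variables text alone would have no instruction to weigh the infant at the visit, and a weight not taken then can be recovered only if a dated record exists elsewhere.

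The outcome has a purpose of its own. According to Participant timeline, one of the three 10-week programme sessions runs post-partum, and weight at the postnatal visit is the only listed infant growth outcome late enough to reflect it.

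A second, smaller matter follows once the weight is collected. Infants gain weight over the four-week visit window. A raw comparison therefore carries variation due only to the date of the visit, and the article's generic tests do nothing to remove it.

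**Working it through.** **1. The plan's own figure.** The only design calculation is for the primary endpoint: 50% against 40%, two-sided 5%, power 80%.

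- n per arm = [1.960 × √(2 × 0.45 × 0.55) + 0.842 × √(0.5 × 0.5 + 0.4 × 0.6)]² / 0.10² ≈ 387.3, that is 388 when rounded up, against 387 stated. Power at 387 per arm is 0.7997.
- 774 / (1 − 0.10) = 860, as stated.

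The sample size reproduces, and nothing below changes it.

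**2. Infant weight, side by side.**

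| Time | Outcome sections | Clinical variables |
|---|---|---|
| Birth, first 24 h | Birth weight, macrosomia, neonatal adiposity | Weight, length, skinfolds within 24 h; length and weight again, at birth |
| Postnatal visit, 6 to 10 weeks | Child weight; number with excessive weight | Mother's weight and height; child's health since birth; no infant weight named |

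Birth is covered twice and the visit not at all. The second birth sentence stands at the end of the block on the postnatal visit and gives infant adiposity as its purpose, whereas the 24-hour sentence already covers neonatal growth and adiposity. The most natural explanation is that the visit was meant.

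**3. What the visit window adds to raw weight.** The documents give no infant growth rate and no SD of infant weight, so these inputs are assumptions: weekly gain g = 0.15 to 0.25 kg, and SD at a fixed age s = 0.5 to 0.7 kg. The spread of age at the visit, a, is 4/√12 = 1.155 weeks if visits are even over 6 to 10 weeks, or 0.6 week if they cluster near 8 weeks (also assumed).

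Relative increase in variance = (g × a)² / s².

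- Low: (0.15 × 0.6)² / 0.7² = 0.0081 / 0.49 = 1.7%.
- Mid: (0.20 × 1.155)² / 0.6² = 0.0533 / 0.36 = 15%. The SD rises from 0.60 to √(0.36 + 0.0533) = 0.64 kg.
- High: (0.25 × 1.155)² / 0.5² = 0.0833 / 0.25 = 33%.

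A gain of 0.30 kg/week with s = 0.6 also gives 33% (0.12 / 0.36). Only the corner that pairs 0.30 kg/week with the smallest SD goes further: 0.12 / 0.25 = 48%.

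**4. Effect on precision, taking 387 per arm.** Detectable difference at 80% power = (1.960 + 0.842) × SD × √(2/387).

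- Mid case: 0.121 kg without timing noise, 0.129 kg with it. Power for a difference of 0.121 kg falls from 80% to 74%.
- Over the grid with g up to 0.25 kg/week: power between 68% and 79%. If visits cluster near 8 weeks, the variance increase is 2% to 9% and power stays at about 77% to 79%.

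**The case against.** The strongest reply is that this is a misprint in a condensed article. The sentence sits in the postnatal block, the Endpoints section gives child weight its own timing, and that timing agrees with the visit window. The schedule of assessments (Table 1) and the eCRF are not shown, and either may list the measurement. Nor is the Clinical variables section a complete list: it omits gestational age at birth and respiratory distress, which are also endpoints and are surely collected. All of this stands against a claim that the data are missing. It does not remove the conflict, because for infant weight the article does more than stay silent: it states a time, and that time is wrong for the outcome.

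On the analysis, one can fairly say that the tests are generic and that a detailed analysis plan is promised before database lock. Age standardisation may be intended there. The cut-off for excessive weight and the handling of missed visits are properly left to that plan or to the full protocol, and are no finding here.

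Three stronger readings are tempting, and the documents do not support them:

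- *That none of the 860 infants will have the outcome.* This follows only if the text is applied literally and nothing else instructs the sites.
- *That the safety of the child cannot be assessed.* The article ties safety to details of health since birth, which are still obtained at the visit.
- *That visit timing biases the comparison.* That needs mean age at the visit to differ between arms. Allocation is 1:1 and stratified by center, and both arms attend the same usual-care visit. The trial is open, so a difference cannot be excluded, but nothing in the article points to one.

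**Conclusion.** The inconsistency is real and rests on the text alone: the outcome is set at the postnatal visit, while both stated infant measurements are at birth. It is probably a drafting slip. What is shown is an instruction that conflicts with an endpoint, not lost data.

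The case for age standardisation is sound but secondary. It is worth roughly 2% to 33% of the variance of raw weight, about 15% in the mid case, on assumed growth, SD and visit spread, and somewhat more only in the extreme corner shown above. That is a modest loss of precision on a secondary endpoint, with bias only if visit timing differs between arms. The primary endpoint and the 774 and 860 figures stand.

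**What to change.** 1. Reconcile the last sentence of Clinical variables with the Abstract, Background and Endpoints, so that infant weight and length are recorded, with the date, at the existing postnatal visit.
2. Confirm that Table 1 and the eCRF carry infant weight, length and measurement date at that visit, and add any that are absent.
3. State in the analysis plan that infant weight at the visit is compared as a weight-for-age z-score by sex and exact age, or as weight adjusted for age at the visit, in place of the unadjusted test on raw weight.

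The cost is one corrected sentence, a check of the eCRF with at most three fields to add, and a line in the analysis plan. No extra visit and no change to the sample size are needed.

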#### Online assessments

Information on diet habits, eating behaviors, physical activity, motivation stage is collected through self-administered validated questionnaires. The Short Dietary Questionnaire (SDQ) estimates energy nutrient and food intakes based on 14 items of food frequency consumption [32]. The Three Factors Eating Questionnaire (TFEQ) [33] is a food intake-behavior related questionnaire, which contains 21 items and measures three dimensions of eating behavior (cognitive restraint of eating, emotional eating, and uncontrolled eating). The Pregnancy Physical Activity Questionnaire (PPAQ) [34] is a questionnaire of 36 items enable to evaluate the duration, frequency, and intensity of physical activities in pregnant women. The motivation stage is estimated by questioning on the stage of changing [35] in order to follow a healthier diet and practice more physical activity. It contains two 5 stage-questions (see supplemental material). Questionnaires are filled three times during the trial, at the inclusion (between 22 and 25 weeks), at the mid-course of the intervention (between 32 and 35 weeks) and after delivery (up to 10 weeks’ post-partum).

### Data management

The data collected along the visits are entered through an electronic case report form (eCRF) using Clinsight software. The data of the participants collected from the web-based platform (through the self-administered questionnaires) are protected by a secured access. The data are stored in a secured server provided by Bepatient™.

### Statistics

Statistical analyses will be independently performed by the Biostatistics Department of University of Lille. Data will be analyzed using the SAS software (SAS Institute Inc., Cary, NC, USA) and all statistical tests will be performed with a 2-tailed alpha risk of 0.05. A detailed statistical analysis plan will be written and finalized prior to the database lock. For each exploratory analysis, a statistical analysis plans will be provided before any data analysis. Baseline characteristics will be described for each group. Quantitative variables will be expressed as mean (± standard deviation), median (± interquartile range) and 95% confident interval. Qualitative variables will be expressed as frequencies and percentages. Normality of distribution will be assessed graphically and using the Shapiro-Wilk test. The primary analysis for primary and secondary endpoints will be conducted on the intention-to-treat principle. A secondary per-protocol analysis will be performed.

The primary endpoint (rate of delivery interventions) will be compared between the two groups using the Chi-square test. Absolute and relative risk difference (intervention vs. control) and their 95% confidence intervals will be calculated. For the secondary objectives, binary endpoints will be compared between the two groups using chi-square tests or Fisher’s exact tests when the expected cell frequency will be inferior to 5. Quantitative endpoints will be compared between the two groups using student *t* tests or Mann-Whitney U tests in case of non-normal distribution (except if a log-transformation can be applied to normalize the data). For quantitative endpoints involving repeated measures, a linear mixed model will be used. This model allows to perform an ANOVA for repeated measures taking into account the correlation between the repeated measures. The choice of the covariance in the models will be based on the AIC criteria and normality of residuals will be checked.

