## Methods

### Study setting

ePPOP-ID is an open multicenter randomized controlled trial, which involves 18 university and/or regional hospitals from nine regions in France (study design illustrated in Fig. 1 and Table 1). These centers deliver approximately 30,000 patients per year, which leads to a potential of 2400 to 3000 obese pregnant women per year (i.e. 8 to 10% of the pregnant women being obese), which makes 200 to 250 eligible women per month.

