### Randomization

The randomization procedure is performed at the end of the inclusion visit, centralized and stratified by center. The 1:1 assignment sequence (based on blocks of four and the use of a computer random-number generator) is produced by the sponsor. The randomization list is not disclosed to the study centers, monitors, statisticians or to the trial team. After collection of the email address of participants, an invitation is sent to each participant to connect to the web-based platform, in order to complete the registration procedure (i.e. to complete the profile and define a login password), as well as fill in the online initial assessments. The intervention group also has access to the personalized electronic lifestyle program whereas the control group not. Due to the nature of the intervention a blind study was not achievable.

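### A free gain in precision is left unused: the primary chi-square test ignores centre, although allocation is stratified by it, and ignores baseline history

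*Protocol article*

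**What the plan says.** On the primary analysis, the Statistics section of the Protocol article states: "The primary endpoint (rate of delivery interventions) will be compared between the two groups using the Chi-square test". It adds "Absolute and relative risk difference (intervention vs. control) and their 95% confidence intervals will be calculated". Neither sentence mentions centre or any baseline variable. The Sample size section uses the same test, two-sided at 5% with 80% power, for 50% against 40%. It arrives at 387 women per group, 774 in total, and 860 after allowing for 10% drop-out or missing data.

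On allocation, the Randomization section says "The randomization procedure is performed at the end of the inclusion visit, centralized and stratified by center", and "The 1:1 assignment sequence (based on blocks of four and the use of a computer random-number generator) is produced by the sponsor". The Study setting section describes a trial "which involves 18 university and/or regional hospitals from nine regions in France".

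On baseline data, the Clinical variables part of Data collection says "At inclusion visit between 12 and 22 weeks, demography, medical and family history and current pregnancy health information are collected", and then "Anthropometric variables (weight and height) are measured; blood and urine samples are drawn". Parity and previous caesarean are not named there or anywhere else in the article. The eligibility criteria exclude women on neither ground.

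**The concern.** Stratified allocation balances the arms within each centre. If centres differ in their rates of caesarean and instrumental delivery, that balance makes the difference between arms less variable than under unrestricted allocation. A chi-square test that ignores centre takes no credit for this: its standard error stays at the unrestricted value and is somewhat too large.

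The second issue is separate. The eligibility criteria allow women of any parity, with or without a previous caesarean, so risk of the endpoint may vary widely at baseline. A crude comparison leaves that variation in the error term. It remains valid, but an analysis using the same women could be more precise.

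This matters because there is no margin. Power is 80% only if the full ten-point fall occurs, and the article's own background cites a review that found no evidence of an effect on caesarean rates.

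**Working it through.** **1. The plan's own figure.** Inputs from the Sample size section: 50% and 40%, so the mean is 45%; z-values 1.960 and 0.842.

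n per arm = [1.960 × √(2 × 0.45 × 0.55) + 0.842 × √(0.25 + 0.24)]² / 0.10² = [1.379 + 0.589]² / 0.01 = 387.3.

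This reproduces 387 (388 if rounded up). Also, 774 / 0.90 = 860. Power at 387 per arm is Φ[(0.10 × √387 − 1.379) / 0.70] = Φ(0.840) = 79.97%. The test and the sample size agree.

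**2. Baseline predictors.** On the risk-difference scale, adjustment multiplies the variance by about (1 − R²), where R² is the share of outcome variance explained. Effective n per arm is then 387 / (1 − R²), and the 95% CI half-width is 1.96 × √[(0.49 / 387) × (1 − R²)]. The article gives no R², so every row after the first is an assumption.

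| Assumed R² | Power | CI half-width (points) |
|---|---|---|
| 0 | 80.0% | 6.97 |
| 0.02 | 80.8% | 6.90 |
| 0.05 | 82.0% | 6.80 |
| 0.10 | 84.0% | 6.62 |
| 0.15 | 86.0% | 6.43 |
| 0.20 | 87.9% | 6.24 |

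Expressed as evaluable women, 774 / (1 − R²) − 774 is about 16 at R² = 0.02 and about 194 at R² = 0.20.

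To show what R² = 0.15 requires, suppose 20% of women have a previous caesarean and a risk of 75%, 40% are nulliparous at 60%, and 40% are other multiparous women at 27.5%. The mean is 0.15 + 0.24 + 0.11 = 0.50. The between-group variance is 0.2 × 0.25² + 0.4 × 0.10² + 0.4 × 0.225² = 0.03675, and 0.03675 / 0.25 = 0.147. These risks are assumed and do not come from the article.

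**3. Centre, by simulation.** Set-up: 18 centres of 43 women (774), 1:1 within centre, 3000 trials per scenario, marginal rates held at 50% and 40%. The between-centre SD on the logit scale is assumed, as is one binary baseline predictor. The adjusted analyses are linear risk-difference models with robust standard errors. Entries are power for chi-square / centre-adjusted / centre plus predictor.

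| Predictor (odds ratio, prevalence) | Centre SD 0 | Centre SD 0.3 | Centre SD 0.5 |
|---|---|---|---|
| none | 80.2 / 80.4 / 80.5 | 80.3 / 81.0 / 81.0 | 81.4 / 82.8 / 83.1 |
| 2.7, 40% | 81.1 / 81.2 / 82.8 | 79.6 / 80.2 / 83.1 | 79.7 / 81.6 / 83.7 |
| 4.5, 40% | 80.7 / 80.9 / 85.5 | 79.2 / 80.1 / 84.4 | 80.7 / 82.1 / 86.1 |
| 7.4, 20% | 79.7 / 80.3 / 84.6 | 79.0 / 79.9 / 85.6 | 81.1 / 82.4 / 86.8 |

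Centre alone adds about 0 to 2 points. With centre SD 0.5 and no predictor, the mean unadjusted standard error is 0.0355 and the centre-adjusted one 0.0346, a ratio of about 1.026. The actual sampling SD in that scenario is 0.0345, so it is the unadjusted figure that is too large.

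Under no effect and centre SD 0.5, the chi-square rejected in 4.1% to 4.6% of trials and the adjusted analyses in 4.8% to 5.5%. Monte Carlo error is about 0.4 points.

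**The case against.** The strongest reply is that nothing is wrong as written. Test and sample size match, power is as planned, and the test errs slightly on the conservative side. Chance imbalance is already allowed for in a randomised test's error rate. All of that stands, and it rules out three stronger readings that a reader might infer:

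- *The trial is underpowered.* It is not, under its own assumptions. Power is lower only in comparison with an adjusted analysis.
- *The confidence intervals are too wide in general.* Strictly, this holds only through the omitted stratification factor, and the effect is small. For omitted baseline predictors the crude interval is correct, only less efficient.
- *Strong predictors of delivery mode are known to be collected.* The article lists broad categories of history. Parity and previous caesarean are a reasonable inference, but their presence in the case report form and their strength are not stated. Nor does the article say how far delivery rates differ between the centres.

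It can also be said that a detailed SAP is promised before database lock and is not shown. Supplementary adjusted analyses may well be in it, and their absence from the article is no finding. But the article does name the primary test, so the point is about a stated choice and not about a gap.

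Finally, the simulation used a linear model with robust errors and not the logistic model proposed below. The gains should carry over approximately, but that model was not itself simulated.

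**Conclusion.** The point stands as an efficiency and alignment weakness that costs almost nothing to repair. Analysis by the randomisation strata is worth little by itself: about 0 to 2 power points, with the unadjusted standard error 0% to about 2.5% too large, for an assumed centre SD of 0 to 0.5 on the logit scale. Most of the possible gain lies in baseline predictors. For an assumed R² of 0.02 to 0.20, power rises from 80% to about 81% to 88%, and intervals narrow by roughly 1% to 10.5%. If the available predictors are weak, the gain is a point or two. Confidence is high for the direction and moderate for the size, because none of the prognostic strengths comes from the article.

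**What to change.** Before database lock, and before any outcome data are seen by arm, prespecify the following in the SAP and record it as a change to the published primary analysis:

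- A primary logistic model with arm, centre (random intercept, or small centres pooled by a stated rule) and a short named list of baseline predictors. A natural candidate is a three-level factor: nulliparous; multiparous without previous caesarean; multiparous with previous caesarean. The sponsor should first confirm that these items are recorded at inclusion. If only centre is to be used, Cochran-Mantel-Haenszel is enough.
- The marginal (standardised) risk difference and risk ratio with 95% CI as the reported effects, so that the quantities the article already promises keep their meaning.
- The crude chi-square as a supportive analysis.

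The trial is open, so predictors chosen after results are visible would not be credible. The list should therefore be fixed now. The cost is wording in the Statistics section and the SAP. No extra women or visits are needed, and no new data if parity and previous caesarean are already in the inclusion history.
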